### EMG data processing

All EMG data will be sampled at 1000 Hz and be filtered post-processing using a Butterworth fourth-order band pass filter (10–500 Hz). The EMG will be full wave rectified and normalized to the peak EMG recorded for each muscle. The EMG will then be aligned with the selected gait cycles and temporally normalized to 100% of the cycle. EMG will then be averaged across all gait cycles for the left and right sides. Such methods will reduce the subject-specific and situation-specific conditions that may result in signal variance. The activation profiles of each of the muscles will be assessed, including EMG onset and offset time; duration and timing of muscle activity; average time to peak muscle activation; and total burst activation (integral of rectified EMG).

The gait and EMG data processing will be conducted by the principal researcher, and all of the research team will have access to the final trial dataset.

### Statistical analysis

Sample characteristics will be summarized into the number of non-missing data, mean, standard deviation, minimum, maximum and 95% confidence interval, for quantitative variables. Number of non-missing data, frequency and proportion will be used for the description of categorical variables.

Gait speed will be the primary outcome in this study. The possible effects of participants’ physical activity level at baseline on gait speed will be investigated by performing an analysis of the Pearson correlation between gait speed (estimated using the Vicon system before applying tDCS) and physical activity level.

We will examine the within-visit effects of each tDCS on gait speed as the primary outcome and the gait kinematics and TUG time as secondary outcomes using a paired *t* test to compare pre- and post-tDSC measures.

The main effect of the three tDCS conditions (monopolar bilateral tDCS, bipolar bilateral tDCS and sham tDCS) on gait speed and gait kinematics will be examined through a linear mixed model (LMM) with random intercepts. The LMM model will contain participants nested in sequence as a random effect. In order to investigate the carry-over effect, we will compare three measures before the three tDCS procedures using one-way analysis of variance (ANOVA). When appropriate, post hoc comparisons will be carried out using a Tukey correction for multiple comparisons. The LMM will also be conducted to examine the potential interaction of time (levels: pre- and post-tDCS) and tDCS (levels: monopolar bilateral tDCS, bipolar bilateral tDCS and sham tDCS) in the two conditions of even and uneven surfaces. *P* values less than 0.05 will be considered significant, and for valid interpretation of the results the confidence interval will be reported as an indication of effect size [63]. All analysis will be performed using SPSS software (version 23; IBM Corporation, Armonk, NY, USA). Missing data will be handled using a simple imputation method [58]. This Statistical Analysis Plan (SAP) will be provided before opening the database.

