In the present study, we will address this issue by systematically investigating the effects of a-tDCS over the premotor and primary motor cortices and the synergetic effects of a-tDCS over the premotor and primary motor cortices and c-tDCS over the cerebellum. As it is thought that tDCS is most effective when combined with a behavioural task [36], tDCS will be administered during simultaneous treadmill walking, because a recent study reported more pronounced effects after this task compared to other physical tasks in PD [37]. This ensures that the neural circuits, and particularly M1, are active during application of the tDCS. In this study, we also took advantage of the same anode electrode parameters used in studies by Kaski et al. [30, 33, 35, 38]. Applying bilateral a-tDCS over the premotor and primary motor cortices and comparing the effects of both active (small) and functionally inert (large) cathodes over the cerebellum in PD could disentangle the location of possible tDCS effects on gait abilities in PD. We hypothesize that a large cathode will render stimulation over the cerebellum inactive (i.e. a monopolar M1 set-up), whereas a smaller cathode will exert additional inhibitory effects on the cerebellum (i.e. a bipolar M1 cerebellar set-up) [39]. To our knowledge, no study to date has analysed the gait parameters and electromyography (EMG) of the lower limb focusing specifically on different bilateral tDCS montages.

Thus, this randomized placebo (“sham tDCS)” controlled study aims to examine the short-term effects of (1) monopolar bilateral a-tDCS over the premotor and primary motor cortices (exploratory aim 1); (2) bipolar bilateral a-tDCS over the premotor and primary motor cortices and cerebellum cortex (exploratory aim 2) while walking on a treadmill on gait speed as the main outcome measure and other gait kinematics and EMG in people with PD when optimally medicated. The findings will be reported and disseminated through peer-reviewed journal publication and conference presentations. The results of the study will also be presented for PD support groups who contributed in participant recruitment.

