### Primary and secondary outcomes

The primary outcome will be gait speed, and secondary outcomes include other gait kinematics, muscle activation and functional mobility (Table 1).

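### TUG time is assigned only uncontrolled pre/post paired t tests, and the protocol does not say which of three analyses decides gait speed

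*Protocol article*

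**What the plan says.** The Abstract lists TUG among the secondary outcomes. The section on primary and secondary outcomes agrees: "secondary outcomes include other gait kinematics, muscle activation and functional mobility (Table 1"), and Table 1 gives TUG as the mobility instrument.

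The Statistical analysis section then assigns outcomes to methods in three steps.

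- **Within-visit tests.** "We will examine the within-visit effects of each tDCS on gait speed as the primary outcome and the gait kinematics and TUG time". The method is a paired t test of the values before stimulation against those after it. Gait speed, kinematics and TUG are all included.
- **Three-condition mixed model.** The comparison of monopolar, bipolar and sham stimulation "on gait speed and gait kinematics will be examined through a linear mixed model (LMM) with random intercepts". TUG is not listed. Tukey post hoc comparisons follow where appropriate.
- **Interaction model.** The mixed model also serves to test whether change over time differs by stimulation condition, with sham as one level. This is to be done "in the two conditions of even and uneven surfaces". No outcome is named.

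One significance rule, P < 0.05, covers all three. The section on the intervention states that participants walk on the treadmill under both active and sham stimulation. The Background explains that treadmill walking was chosen "because a recent study reported more pronounced effects after this task compared to other physical tasks in PD".

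**The concern.** A pre/post change within one session contains everything that happened in that session: stimulation, 20 minutes of treadmill walking, warm-up, fatigue and familiarity with the test. Sham stimulation is in the design to remove all but the first, and it can do so only if the analysis compares active with sham. For TUG the stated analysis does not. Practice is plausible there, because the dual-task trial repeats counting backwards in threes before and after stimulation.

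For gait speed the concern is milder. A controlled test is planned, but it is one of three analyses with no stated order, and the only analysis sentence that calls gait speed the primary outcome is the one on paired tests. That leaves room to read a significant change under active stimulation and a non-significant one under sham as efficacy. Such a pattern is not a test of the difference between the two.

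**Working it through.** **Step 1: does any sham comparison reach TUG?**

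| Analysis | Outcomes named | Sham compared with active? | Covers TUG? |
|---|---|---|---|
| Paired t test, pre v post | Gait speed, kinematics, TUG | No (one test per condition) | Yes |
| Mixed model, three conditions | Gait speed, kinematics | Yes | No |
| Time by tDCS interaction | None; set on even and uneven surfaces | Yes | No |

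The surfaces in the last row belong to the six walkway walks in the section on three-dimensional gait assessment. The TUG section describes a practice trial, then one single-task and one dual-task trial, with no surface factor. So no stated analysis compares TUG under active stimulation with TUG under sham.

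**Step 2: how often would a paired test be positive with no tDCS effect?** The plan gives no figure for this, so there is none to reproduce.

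Inputs:
- n = 18, from the Sample size section.
- Two-sided 0.05. The level is in the plan; two-sidedness is assumed.
- A gain g of 0.03, 0.04 or 0.05 m/s, common to all three conditions. Assumed.
- SD of within-person change 0.06 m/s. Assumed. No SD is stated; 0.06 is close to the SD of a paired difference that would give the planned 18 (delta 0.05, 80% power: 14 completers, and 14/0.8 = 17.5, rounded up to 18). That SD need not equal the SD of a within-visit change, so it is only a rough anchor.
- Changes independent across visits. Assumed.

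The test statistic follows a non-central t with 17 degrees of freedom, critical value 2.110, and non-centrality (g/SD) × √18.

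| g (m/s) | g/SD | Non-centrality | P(one paired test significant) = p |
|---|---|---|---|
| 0.03 | 0.50 | 2.12 | 0.516 |
| 0.04 | 0.67 | 2.83 | 0.760 |
| 0.05 | 0.83 | 3.54 | 0.915 |

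Only g/SD matters, so the same probabilities apply to TUG in seconds for the same ratio. The result moves with the SD: at g = 0.05, p runs from 0.98 (SD 0.05) to 0.52 (SD 0.10).

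**Step 3: how often does the misleading pattern arise?** For one given active condition significant and sham not, the probability is p(1 − p). For at least one of the two active conditions it is [1 − (1 − p)²](1 − p).

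| g (m/s) | One given active, not sham | At least one active, not sham |
|---|---|---|
| 0.03 | 0.516 × 0.484 = 0.25 | 0.766 × 0.484 = 0.37 |
| 0.04 | 0.760 × 0.240 = 0.18 | 0.942 × 0.240 = 0.23 |
| 0.05 | 0.915 × 0.085 = 0.08 | 0.993 × 0.085 = 0.08 |

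**Step 4: the controlled contrast.** A shared gain cancels in active-minus-sham change, so that test keeps its nominal size. Simulation with the inputs above gave 0.050 to 0.051 at all three gains.

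**The case against.** Three stronger readings are tempting, and the document supports none of them.

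- **That efficacy as a whole is to be judged by uncontrolled tests.** It is not. Gait speed and kinematics have a mixed model with sham as a level, Tukey comparisons and a time by tDCS interaction, which is the right kind of test. The sample size is also framed on the difference between active and sham. That the paired tests come first is order of mention, not a stated hierarchy.
- **That treadmill practice would be reported as a tDCS effect.** The paired test applies to each condition, and the section counts sham as one of the three. A shared gain would tend to show in the sham session as well, and a careful reader would see it. The support extends only to saying that it could be misread.
- **That identical conditions would give discordant verdicts about half the time.** That holds only near 50% power (2 × 0.5 × 0.5). At p = 0.915 it is 2 × 0.915 × 0.085 = 0.16, and half of that runs in the harmless direction.

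It is also fair to say that TUG is one secondary outcome, that the article is condensed, and that a separate analysis plan is mentioned and might place TUG elsewhere. This limits the weight of the point but does not remove it: the article does not leave the TUG test open, it assigns one, and the one assigned is uncontrolled. EMG is different. The section names no analysis for it, which is detail an article may leave to the analysis plan, and it is not part of this point.

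**Conclusion.** The point holds for TUG: as written, a named secondary outcome in a sham-controlled trial is never compared with sham, and its analysis cannot separate tDCS from practice, warm-up or fatigue. This follows from the text and needs no assumption.

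For gait speed and kinematics it holds only as an ambiguity. Controlled analyses exist, but the protocol does not say which result decides. The figures are illustrative. With no tDCS effect and n = 18, each paired test is positive with probability 0.52 to 0.92, against about 0.05 for the controlled contrast. At least one active condition is significant with sham not significant with probability 0.37 down to 0.08. All of this rests on an assumed common gain of 0.03 to 0.05 m/s, an assumed SD of 0.06 m/s and independence across visits. The documents give neither a practice gain nor an SD.

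**What to change.** Make three changes to the Statistical analysis section.

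1. Analyse single-task and dual-task TUG with the same mixed model, using the time by tDCS interaction or active-minus-sham change, without the surface factor.
2. Name the time by tDCS contrast of each active montage against sham as the deciding analysis for gait speed.
3. Report within-visit changes by condition as means with 95% confidence intervals, labelled descriptive, and not as tests of efficacy.

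The cost is analysis wording only. TUG is already measured before and after stimulation in every session, sham included, so no new data are needed.

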## Methods

### Study design and outline

The study will employ a randomized, double-blind, sham-controlled cross-over design to assess the effect of a-tDCS delivered during treadmill walking on natural overground gait performance and associated muscle activation. Participants will receive bilateral active or sham tDCS for 20 min while walking on a treadmill over three sessions. Gait will be assessed using a three-dimensional (3D) motion capture system and EMG before and after applying tDCS in each session. All assessment will be conducted by the principal researcher, who was trained for conducting all the assessments. The overall study design is illustrated in Fig. 1. A Standard Protocol Items: Recommendations for Interventional Trials (SPIRIT) schedule is presented in Fig. 2, and a SPIRIT checklist is available in Additional file 1. The steering committee is the supervisory panel for the principal researcher, and data monitoring is done by the Research Method Advisory Group in the Institute of Health and Biomedical Innovation (IHBI) at Queensland University of Technology (QUT). The trial will be monitored on a weekly basis by the supervisory panel. The Institutional Human Research Ethics Committee approved the research. The ethics committee will be informed of any trial modifications, and these updates will be made to the trial information on the Australian New Zealand Clinical Trials Registry website. The study will be undertaken and reported based on the Consolidated Standards of Reporting Trials (CONSORT) statement for non-pharmacological treatment.

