### Clinical baseline assessment

Eligible participants will be asked to perform further clinical assessments, including:Visual function including contrast sensitivity and visual acuity. Contrast sensitivity will be assessed using the Pelli-Robson chart with normal values of 1.80–2.10 at both 1 and 3 m distance for persons 40–59 years old, and 1.65–1.95 at 1 m and 1.65–2.10 at 3 m for those ≥60 years old [42] ; and the Melbourne Edge Test, where abnormal values differ for different age groups ranging from < 22 in individuals younger than 50 years to < 14 in individuals older than 80 years old [43]. Visual acuity will be assessed using the Bailey-Lovie chart set, where the values of the logarithm of the minimum angle of resolution (logMAR) range from normal (− 0.3) to poor (1.00) [44, 45].Lower limb peripheral sensation (internal and external malleolus, distal phalanx of third toe, arch of foot, heel and dorsum of proximal phalanx of toe) will be assessed using a Semmes-Weinstein-type pressure aesthesiometer; the lower tactile threshold score, the better [46].Mobility will be assessed using the Tinetti balance and gait test, whereby a value ≤18 suggests high risk for falls and ≥ 24 suggests low risk for falls [47].

Following the clinical assessments, questionnaires will be provided to the participants to be completed at their convenience at home, including demographic information, the International Physical Activity Questionnaire (IPAQ) [48], the Activities-specific Balance Confidence (ABC) Scale [49], a medication diary to calculate levodopa equivalent daily dose, quality of life questionnaires (Parkinson’s Disease Questionnaire (PDQ-39) [50], Parkinson’s diseases gait and falls questionnaire [51] and the UPDRS (Part 2: activities of daily living; patient questionnaire section) [52]. All questionnaires have good psychometric properties and have been used in previous PD trials [3].The participants will be asked to attend the gait laboratory for three visits with at least a 1-week interval between them and to return the completed questionnaires on the first visit. The assessments and the time points and all outcome measures at which the assessments will be taken are presented in Table 1. All questionnares and forms will be found in the online thesis, which will be available via the QUT library.

**Table 1 Tab1:** Baseline and follow-up outcome measures

Outcome measure	Instrument	To be completed at convenient time	Visit 1		Visits 2–4
			Screening	Clinical	

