#### Blinding and randomization

Blinding of the principal researcher will be achieved by using the “study mode” of the DC stimulator. The study mode activates active and sham stimulation with digital codes. To minimize biasing the outcomes, an independent researcher creates a list of participants using block randomization. A randomization sequence is produced through random permutations generated by a stochastic process program in R software version 3.3.4. The size of the blocks will be set to 3 with a ratio of 1:1 so that we need six blocks of the collection (1. ABC, 2. BAC, 3. BCA, 4. CBA, 5. CAB, 6. ACB). We will draw six numbers randomly and sequentially from this collection.

In the randomization list the preprogrammed digital codes of tDCS and the size of the cathode electrode will be assigned to each participant for each session and submitted to the principal researcher via a sealed envelope. The independent researcher provides the digital code and cathode electrode size for the principal researcher prior to each tDCS session. The DC stimulator display continues to indicate the impedance and the time in the same fashion for both active and sham tDCS. The principal investigator will be blinded to the participant and experimental condition during the processing and analysing of the gait data. However, in the case of an adverse event, where it is necessary for the principal researcher to know which stimulation the participant is receiving, the principal researcher will be unblinded. Data from the identifiers will be removed and replaced by codes. However, the data will be re-identifiable by using the code or linking the participant’s details to their allocation and to their different datasets. Reliability of blinding will also be assessed after each tDCS session by asking participants about the type of stimulation they believed they had received [58]. The principal investigator will also guess and record which stimulation type the participant had received.

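### The time-by-tDCS mixed model states only a participant random effect, so if gait speed varies from day to day its test is too conservative; a condition main effect read from stacked pre and post rows would be halved, with too small a standard error

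*Protocol article*

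**What the plan says.** All of this is in the protocol article. Under Study design and outline, gait is measured "before and after applying tDCS in each session". Clinical baseline assessment sets "three visits with at least a 1-week interval between them". Blinding and randomization lists six orders of the three conditions: "1. ABC, 2. BAC, 3. BCA, 4. CBA, 5. CAB, 6. ACB".

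Statistical analysis then plans three looks at gait speed:

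- within-visit comparisons "using a paired *t* test to compare pre- and post-tDSC measures";
- a main effect of condition that "will be examined through a linear mixed model (LMM) with random intercepts", with the random part given as "The LMM model will contain participants nested in sequence as a random effect";
- a further use of the model: "The LMM will also be conducted to examine the potential interaction of time (levels: pre- and post-tDCS) and tDCS", on even and uneven surfaces.

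The section does not say whether the response in the main-effect model is the post value, the change, or pre and post rows together. It does not say which of the three looks decides the primary outcome. No participant-by-visit random effect is mentioned.

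**The concern.** The pre and post values of one visit share that day's state (medication response, fatigue, marker placement). Two visits of the same participant do not. A participant intercept makes all six values of a participant equally correlated, so day-to-day variation is put into the residual.

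That matters differently for the two contrasts. The interaction compares changes within a visit, where the day effect cancels, so a residual that contains day variance is too large for it. A condition main effect compares visits, where the day effect does not cancel, so the same residual is too small for it. If pre rows are in the main-effect model, that effect also averages in a value taken before any stimulation. In a trial of 18 people, either fault could decide the result.

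**Working it through.** **Inputs from the article.** 18 participants, 5% level, 80% power, delta 0.05 and 20% drop-out (Sample size); three visits with a pre and a post value each; six sequences, taken as balanced. The unit of delta is not stated; m/s is assumed. No SD is given, so the day SD (d) and residual SD (e) below are assumptions.

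**The plan's own figure.** The 18 cannot be reproduced without an SD. Back-solving: 18 × 0.8 = 14.4, so about 14 evaluable. A two-sided paired t test with 14 pairs and 80% power needs delta/SD = 0.810, so the SD of paired differences is 0.05/0.810 = 0.062 m/s. This does not show how variance splits between day and residual.

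**Model.** Value = participant + day (variance d²) + residual (variance e²), with r = d²/e² and n = 18.

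1. True variance of a pairwise contrast.
   - Main effect, mean of pre and post per visit: 2(d² + e²/2)/n = (2d² + e²)/n.
   - Interaction, difference of two changes: 4e²/n.
2. Residual variance under a participant-only intercept. Each participant has five within-person degrees of freedom: two lie between visits (expectation e² + 2d²) and three within visits (e²). The average is e² + 0.8d².
3. Ratio of model SE to true SE.
   - Main effect: √[(1 + 0.8r)/(1 + 2r)].
   - Interaction: √(1 + 0.8r).
4. Size of the main effect. Half of its rows are pre-values, so a true 0.05 appears as 0.05/2 = 0.025.

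**Example, d = e = 0.04, so r = 1.** True interaction SE = √(4 × 0.0016/18) = 0.0189. Model SE = 0.0189 × √1.8 = 0.0189 × 1.342 = 0.0253. A nominal 1.96 then acts as 1.96 × 1.342 = 2.63, a type I error of about 1%. For the main effect the ratio is √(1.8/3) = 0.775; 1.96 × 0.775 = 1.52, a type I error of about 13%.

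**Simulation of pairwise contrasts** (20,000 trials per row, true effect 0.05 for power):

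| d | e | Main-effect SE ratio | Main-effect type I | Interaction SE ratio | Interaction type I | Interaction power: as stated v session respected |
|---|---|---|---|---|---|---|
| 0 | 0.04 | 1.00 | 5% | 1.00 | 5% | 74% v 74% |
| 0.02 | 0.04 | 0.89 | 8% | 1.10 | 3% | 68-69% v 74% |
| 0.04 | 0.04 | 0.77 | 13% | 1.34 | 1% | 50% v 74% |
| 0.05 | 0.03 | 0.70 | 17% | 1.80 | below 1% | 50% v 94% |

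With the session respected, interaction type I error is about 5% in every row.

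**If the main-effect model uses post values only.** Type I error is about 5% at every r and nothing is diluted. Power of the overall condition test (e = 0.05), post only against post adjusted for same-session pre: 85% v 84% at r = 0, 76% v 77% at r = 0.25, 54% v 66% at r = 1, 24% v 58% at r = 4.

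**If visit is left out.** In the post-only model with balanced sequences the estimate stays at 0.050. At r = 1 and e = 0.05, an assumed trend of 0.04 m/s per visit lowers power from about 55% to 39%.

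**The case against.** A reader might infer that the trial's primary model is wrong however it is read: effect diluted, pre-value ignored, error bars wrong in both directions. The article does not support that.

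- It labels no mixed model as primary, only gait speed as the primary outcome.
- The same-session pre-value is not ignored, because the time-by-tDCS model uses it, and its interaction is an undiluted difference in change.
- Halving and a too-small SE require stacked rows in the main-effect model, which the text does not fix. The too-small SE also requires day variance above zero. With post values only, or change scores, a participant intercept gives valid SEs.
- The article need not list every fixed effect. Leaving out visit costs precision but causes no bias under balanced sequences. The visit term and the choice of primary surface can reasonably be left to the full analysis plan.
- Several valid models exist, and part of the gain from adjusting for the pre-value is a gain from a more efficient estimator, not a repair.

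All of this stands. What it leaves untouched is the interaction model: pre and post are its time levels, so the rows are stacked, and the only random term stated is the participant. That is a stated choice, not silence.

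**Conclusion.** The point holds in conditional form. For the planned time-by-tDCS model, any day-to-day variance makes the test conservative. With day and residual SDs of 0.04 m/s, power is about 50% where 74% is available, and type I error is about 1% instead of 5%. With no day variance there is no fault.

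For the condition main effect, the consequence depends on a choice that the article leaves open. Stacked rows give half the effect (0.025 for 0.05) and type I error of about 8% to 17% for day SDs of 0.02 to 0.05 with residual SDs of 0.04 to 0.03. Post values only give a valid test, with a loss of precision that is negligible when day variance is small.

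The direction of each error follows from algebra. The sizes rest on assumed SDs, on m/s as the unit of delta, and on balanced sequences without drop-out.

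**What to change.** Before the database is opened, name one contrast that decides the condition comparison, and fit it in one of two ways:

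- **Preferred:** post-session gait speed as the response; condition, visit and the same-session pre-value as fixed effects; a random participant intercept. Adding each participant's mean pre-value keeps the within-person adjustment separate from differences between people.
- **If pre and post stay stacked:** add a participant-by-visit random intercept, include visit, and read only the time-by-tDCS contrast. Do not interpret the condition main effect.

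Report the pairwise condition contrasts with 95% confidence intervals. No new data are needed, because the pre-value is already collected at every visit. The cost is a change of analysis wording and a few degrees of freedom. If day variance turns out to be nil, little is lost: 85% v 84% power in the check above.

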### Intervention (a-tDCS and sham tDCS) during treadmill walking

The tDCS will be delivered using a portable battery-driven NeuroConn DC Plus stimulator. To ensure that the DC stimulator is not dropped, it is placed on the treadmill panel in front of the participant. Each participant will undergo two active a-tDCS sessions and one sham tDCS session with at least 1 week interval so that we avoid carry-over effects. The washout period in studies into PD and tDCS is varied between 48 h [57] to 1 week. The results of the statistical analysis for testing carry-over effects did not show any of these effects [57]. Therefore, a 1-week interval will be an appropriate washout period.

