### Sample size

In preparation for the development of the protocol, the required sample sizes were calculated using Power Analysis and G* Power version 3.0. based on the primary outcome of gait velocity (measured by a 10-m timed walk, Kaski et al. [30]) and considering previously published cut-points for clinically meaningful difference in gait speed in people with PD: 0.02, 0.06 and 0.1 for small, moderate and large changes respectively [60]. The effect size derived from their study reflects the difference between a-tDCS and sham tDCS combined with physical training on gait velocity. To detect the difference followed by Kaski and considering a significance level of 5%, statistical power at 80%, significance level of 0.05 and delta of 0.05 and allowing for 20% drop-out across the trial, the sample size was calculated to be 18 participants, which allows for a complete cross-over randomization. We will employ some strategies suggested in the study of Little et al. (2012) for limiting data missing during conducting the trial [61].

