One of the possible methodological limitations of this study will be the potential of carry-over effects between testing sessions. Consequently, we will compare the pre-test results of all conditions to ensure they are not significantly different due to possible carry-over effects. Also, we will use a self-selected most comfortable walking speed on the treadmill, which varies in each participant and might result in different activation of M1. Furthermore, we will only assess the acute effects of tDCS on the outcome measures, as long-term effects of a-tDCS on gait abilities were deemed beyond the scope of this study. Nonetheless, this study will inform future studies on the effects of optimal montage of tDCS combined with treadmill walking. If our proposed montage is effective in improving gait in PD, further research needs to be conducted to identify the long-term effects of multiple sessions of tDCS with the same parameters and concurrent accumulation effects of tDCS with other physical tasks. This may offer a significant option for the treatment of PD.

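### The carry-over check groups pre-session measures by the upcoming condition, not the preceding one, and names no participant term, so a non-significant result gives little assurance

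*Protocol article*

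**What the plan says.** The Statistical analysis section fixes the method: "we will compare three measures before the three tDCS procedures using one-way analysis of variance (ANOVA"). It names no participant or repeated-measures term for this test, although the treatment model described just before it has a participant random effect. The general threshold is that P "values less than 0.05 will be considered significant".

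The Discussion, where carry-over is listed as a possible limitation, gives the grouping and the use: "we will compare the pre-test results of all conditions to ensure they are not significantly different due to possible carry-over effects".

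The design facts that matter are these:
- The same people supply all three values: "Each participant will undergo two active a-tDCS sessions and one sham tDCS session with at least 1 week interval" (Intervention section).
- All six orders are used: "1. ABC, 2. BAC, 3. BCA, 4. CBA, 5. CAB, 6. ACB" (Blinding and randomization).
- "the sample size was calculated to be 18 participants, which allows for a complete cross-over randomization" (Sample size).

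**The concern.** There are two separate faults.

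**Grouping.** A pre-session value can carry the effect of the session before it. The plan sorts these values by the session that follows. Each condition's group then mixes first-visit values, which have nothing to carry over, with values that follow each of the other two conditions. Most of the signal is averaged away.

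**Error term.** Three values from each of 18 people are not 54 independent values. An ordinary one-way ANOVA puts the differences between people in walking speed into the error, where they swamp differences between sessions.

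At stake is the assurance drawn from the check. The article names carry-over as a limitation and answers it with this test. A non-significant result would be expected whether or not carry-over of relevant size is present.

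**Working it through.** **Inputs from the article.** 18 participants; three sessions each; six orders; threshold 0.05. Planning delta 0.05: "statistical power at 80%, significance level of 0.05 and delta of 0.05 and allowing for 20% drop-out across the trial". Cut-points for change: "0.02, 0.06 and 0.1 for small, moderate and large changes respectively". No unit is printed beside these figures; they are taken as m/s, the unit for gait speed in Table 1.

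**Assumptions not in the article.** Three participants per order; carry-over λ reaching only the next session; total SD of gait speed 0.20 m/s; within-person correlation (ICC) from 0.5 to 0.95. The article states no SD and gives no operating figure for the carry-over test, so there is no figure of its own to reproduce. As a guide, 18 follows from 14 evaluable participants (14/0.8 = 17.5, rounded up) if the SD of a paired difference is about 0.062–0.064. That is a within-person SD of about 0.064/√2 = 0.045. With a between-person SD of 0.20, the ICC is 0.040/(0.040 + 0.002) = 0.95.

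**Step 1: dilution (no SD needed).** Condition A comes first in ABC and ACB, follows B in BAC and CBA, and follows C in CAB and BCA. Each case is one third of A's 18 pre-values. Hence

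pre-mean(A) = μ + (λ_B + λ_C)/3, and pre-mean(A) − pre-mean(B) = (λ_B − λ_A)/3.

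- Both active montages carry 0.10, sham none: pre-means rise by 0.033, 0.033 and 0.067 (sham). The visible difference is 0.033, with sham higher.
- At 0.05 the visible difference is 0.05/3 = 0.017.
- All three carry 0.10: every mean rises by 0.067 and the difference is zero.

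**Step 2: error term under the ordinary reading.** With no carry-over, the between-condition mean square has expectation σ_w². The error mean square is [34σ_w² + 17(σ_w² + 3σ_b²)]/51 = σ_w² + σ_b². F is therefore centred near 1 − ICC instead of 1: about 0.5 at ICC 0.5 and 0.05 at ICC 0.95.

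**Step 3: simulated rejection rates (%), grouped by upcoming condition.** "Both" means both active montages carry over and sham does not; "one" means a single montage does.

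| ICC | Ordinary, none | Ordinary, both 0.10 | Repeated, both 0.05 | Repeated, both 0.10 | Repeated, both 0.20 | Repeated, one 0.10 |
|---|---|---|---|---|---|---|
| 0.5 | 0.5 | 0.8 | 6 | 7 | 10 | 8 |
| 0.7 | 0.05 | 0.2 | 6 | 8 | 10 | 9 |
| 0.8 | 0.01 | 0.06 | 6 | 9 | 11 | 11 |
| 0.9 | 0 | 0 | 7 | 11 | 10 | 16 |
| 0.95 | 0 | 0 | 8 | 10 | 7 | 22 |

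The ordinary test uses F(2,51) and the repeated-measures test F(2,34). With no carry-over, the repeated-measures form rejects in about 5%. Its power does not climb steadily with λ, because carry-over left unmodelled within a condition's group inflates its own error term.

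**Step 4: a test of the preceding condition**, with participant and visit in the model, F(2,32), both montages carrying over. Power (%):

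| Within-person SD (m/s) | λ 0.05 | λ 0.10 | λ 0.20 |
|---|---|---|---|
| 0.141 (ICC 0.5) | 11 | 33 | 89 |
| 0.110 (0.7) | 16 | 51 | 99 |
| 0.089 (0.8) | 22 | 69 | 99.9 |
| 0.063 (0.9) | 40 | 95 | 100 |
| 0.045 | 69 | 99.9 | 100 |

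**The case against.** **The article never says "between-group".** An ANOVA with one within-person factor is also one-way, and three measures per person fits that. This stands: the ordinary form is the plain reading, not stated text. Under the other reading the near-zero size disappears. The dilution does not, and power stays low.

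**Everything numerical rests on assumed SDs.** True for Steps 3 and 4, which is why ranges are shown. At low correlation the ordinary test moves towards its nominal size: it rejects in 5% of runs without carry-over at ICC 0. The one-third dilution needs no SD, only balanced orders.

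**Comparing baselines by upcoming condition is a fair question in itself.** It asks whether the conditions started level, and an unequal start is what would bias a post-only contrast. This has force. The same dilution also limits the harm: 0.05 m/s carried over in full by both active montages would shift such a contrast by 0.017 m/s against them, below the article's 0.02 for a small change. But the article offers the comparison as its investigation of carry-over, and for that it is poorly aimed.

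**Other protection exists.** Each session has its own pre-measure. The paired pre/post tests and the time-by-condition mixed model remove additive carry-over present at both pre and post. Sessions are at least a week apart, and carrying the full effect across that gap would be extreme. This stands and sets the severity.

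**Two stronger readings are tempting.** One is that the check would certify no carry-over whatever happens. The other is that the treatment comparisons are therefore wrong. The first fails because rejection is not impossible at lower correlation or under the repeated-measures form. The second fails because no analysis or conclusion is made conditional on the check, and because of the pre/post comparisons just described.

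**Conclusion.** The check is poorly specified as written. Grouping by upcoming condition shrinks carry-over differences to one third and reverses their sign, given balanced orders and carry-over to the next session only. Under either reading of the ANOVA, a non-significant result says little about carry-over of 0.05 to 0.10 m/s, which spans the planning delta and the article's large change. If only one montage carries over 0.10 m/s, the repeated-measures form still reaches only about 22% at best over the correlations examined.

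This is a should-fix on an assumption check. The documents do not support calling it an error in the primary estimate.

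**What to change.** Replace the ANOVA with a linear mixed model on pre-session gait speed: random participant, fixed visit (1 to 3), and fixed preceding-session condition (none at visit 1). Report the carry-over differences between conditions with 95% confidence intervals.

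Drop the Discussion's suggestion that non-significance rules carry-over out. Even the better test has only about 11–69% power at 0.05 m/s over the within-person SDs examined, so the intervals should carry the interpretation. State also that carry-over common to all three conditions cannot be separated from a visit effect.

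The cost is one paragraph of analysis wording and a matching sentence in the Discussion. It needs no extra participants or measurements. The article says the analysis plan will be provided before the database is opened, so the change can be made there.
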